### Strategies to improve adherence to interventions {11c}

At each visit, the plasma clozapine concentration is measured to check treatment compliance.

### Relevant concomitant care permitted or prohibited during the trial {11d}

The patients continue their usual medical treatments prescribed by their psychiatrists or their general practitioners. Concurrent use of antipsychotic medication, antidepressants, and lithium is allowed as long as the dose is stable for at least 8 weeks before entering the study. Loxapine (up to 300 mg per day) or hydroxyzine (up to 100 mg per day) may be used to treat anxiety, agitation, or insomnia. Once randomly assigned to one of the groups, the same clozapine dose will be kept throughout the study. The lithium dosage may be adjusted to obtain low levels of lithemia and thus promote tolerance of treatment during ECT. However, patients should not be treated by another electrical or magnetic stimulation method. Anticonvulsant drugs must be stopped (antiepileptics and benzodiazepines) except for lamotrigine. Indeed, lamotrigine is not associated with a decrease in ECT efficacy [11].

### Provisions for post-trial care {30}

No ancillary study is planned for this protocol. At the request of the patients or their psychiatrists, the patients could benefit from new ECT sessions at the end of the protocol.

### Outcomes {12}

#### Main outcome

The main outcome is the response rate assessed by the Positive and Negative Symptoms Scale (PANSS) 3 months after the end of the treatment in patients following the long protocol (i.e., at 15 months) compared to those following the short protocol (i.e., at 9 months), the response being defined as a 30% reduction on the PANSS [12].

#### Secondary outcomes

The secondary outcomes are as follows:
The response rate assessed by the Brief Psychiatric Rating Scale-18 items (BPRS-18) 3 months after the end of the treatment in patients following the long protocol compared to those following the short protocol (the response being defined as a reduction of 30% on the BPRS).The response rates assessed by the PANSS and the BPRS at different times (2, 4, 6, and 12 months) between both groups.The Hamilton Rating Scale-21 items (HAMD-21) score, the Young Mania Rating Scale (YMRS) score, the Modified Overt Aggression Scale (MOAS) score, the Clinical Global Impression (CGI) score, and the Global Assessment Functioning (GAF) score at baseline and at 2, 4, 6, 9, 12, and 15 months. Changes from baseline will be compared between both groups.The Mini-Mental Status Examination (MMSE), the Subjective Scale to Investigate Cognition in Schizophrenia (SSTICS) [13], the RL/RI-16 test assessing verbal memory [14], the Doors test assessing visual memory [15], the D2 Attention Test [16], and the Copy of the Rey-Osterrieth Complex figure test for the evaluation of visuospatial constructional ability [17] at baseline and at 6 and 15 months. Changes between baseline and 6 months and between baseline and 15 months will be compared between the groups.Plasma clozapine concentration measured at baseline and at 2, 4, 6, 9, 12, and 15 months in order to check patient compliance.

### Participant timeline {13}

Experimental design, the time of interventions, and assessments are presented in Figs. 1 and 2.

**Fig. 1 Fig1:**
[figure not shown]
Flow chart of the study design. The main objective was the comparison of the response rate 3 months after the end of each treatment (black circles surrounded)

**Fig. 2 Fig2:**
[figure not shown]
Schedule of enrollment, interventions, and assessments of the study. PANSS, Positive and Negative Symptoms Scale; BPRS, Brief Psychiatric Rating Scale-18 items; MOAS, Modified Overt Aggression Scale; CGI, Clinical Global Impression; GAF, Global Assessment Functioning; HAMD-21, Hamilton Rating Scale-21 items; YMRS, the Young Mania Rating Scale; SSTICS, Subjective Scale to Investigate Cognition in Schizophrenia; MMSE, Mini-Mental Status Examination

### Sample size {14}

The aim of this trial is to compare the response rates between short and long ECT protocols. According to the meta-analysis of Lally et al. [7], the proportion of patients with treatment-resistant schizophrenia that responds to ECT augmentation of clozapine was 61.79% (Table 1: 55/89 cases). However, the relapse following ECT cessation is very high: the relapse rate has been estimated at 62.5% by Kho et al. [18]. On the other hand, Braga et al. [19] suggested that ECT were effective as a continuation strategy to prevent relapse after an acute course of ECT. During the 6-month maintenance period, no patient presented with clinically worsening symptoms. From this literature data, we postulate that the responder rates would be 61.79% in the long ECT protocol and 23.25% in the short ECT protocol (62% × (1 − 0.625) = 23.25%). Assuming an alpha risk of 0.05 and a power of 0.80, we estimated the need to include 25 patients per group. To overcome an estimated 20% drop-out, the required number of patients increased to 32 patients per group. As a result, the total number of participants required for the study is 64 patients.

### Recruitment {15}

Enrollment will occur in 13 clinical centers (Table 1) during 48 months: each center should include 1.2 patients per year, which is far below the usual clinical activity of these centers.

## Assignment of interventions: allocation

### Sequence generation {16a}

Web-based randomization will assign patients to benefit from short or long ECT protocol in a 1:1 ratio with balanced blocks thanks to the Clinsight software. Block size is unknown to investigators. Stratification according to the clinical center will be performed. A file describing the random procedure is confidentially classified within the Biostatistics Unit in the University Hospital of Rouen.

### Concealment mechanism {16b}

On demand, the informed investigator will obtain the patient number and the arm in which the latter has been assigned on the Clinsight website.

### Implementation {16c}

The Biostatistics Unit in the University Hospital of Rouen generated the allocation sequence, which has been downloaded on the Clinsight website. Participants will be enrolled by the investigators of each clinical center (Table 1). However, only informed non-blind investigators will assign participants to an arm.

He then informs the research technician about the organization of the ECT protocol to perform. Among the investigators, the psychiatrist receiving the information of the treatment allocation is different from the psychiatrist who performs clinical assessments.

## Assignment of interventions: blinding

### Who will be blinded {17a}

The investigators, who clinically assessed the patients, and psychologists, who administered cognitive tests, are blinded. The data analysts will be blind until the entire analysis is completed. However, patients and care providers will be informed of the treatment allocation, due to the impossibility of maintaining the blindness in arms with different durations.

### Procedure for unblinding if needed {17b}

As this study is single-blind and an investigator is informed of the arm in each clinical center, the question of revealing the blindness does not arise.

## Data collection and management

### Plans for assessment and collection of outcomes {18a}

As the clinical scales used are part of the current medical practice and are passed by experienced psychiatrists, no training was necessary. The validity and reliability of scales are described in Table 2.

**Table 2 Tab2:** Validity and reliability of the main and secondary outcomes

	Validity	Test-retest reliability and/or sensitivity to change	Inter-rater reliability
Main outcome			
Positive and Negative Syndrome Scale (PANSS) [12]	High internal consistency with an alpha coefficient comprised between 0.73 and 0.83	Reliable test-retest accuracy (0.77 to 0.89)	High correlations, comprised between 0.83 and 0.87
Secondary outcomes			
Brief Psychiatric Rating Scale (BPRS) [20]	Internal consistency: alpha = 0.46 for general score [21]	–	Inter-rater reliability = between 0.87 and 0.97 [22]
Young Mania Rating scale (YMRS) [23]	Concurrent validity: correlation between YMRS and Mania Assessment Scale was very high and statistically significant at each weekly assessment (*r* > 0.91, *p* < 0.001) [24]	Sensitivity to change because there was a statistically significant decline among 15 patients after 2 weeks of treatment [25]	Inter-rater reliability ICC > 0.89 [24]
Modified Overt Aggression Scale (MOAS) [26]	Convergent validity: *r* = 0.75 with history of actual aggressive behavior (*p* < 0.001) Divergent validity: *r* = − 0.09 with Eysenck Personality Questionnaire Extraversion [27]	ICC = 0.6 [28]	ICC = 0.96 [29]
Clinical Global Impression Scale (CGI)-Severity [30]	Positive correlation between CGI-S and HAM-D, anticipatory anxiety, and panic frequency in a sample of 116 patients with panic disorder and depression [31]	–	Inter-rater reliability = 0.66 in 12 patients with dementia [32]
Global Assessment of Functioning scale (GAF) [33]	The multiple regression between the GAF and the measures of symptoms and social behavior were large and highly significant (*r* = − 0.63 with the SANS total and *r* = − 0.46 with the Social Behavior Schedule [34]. A longer hospitalization was associated with lower baseline GAF (OR = 1.91) [35]	–	ICC = 0.89 to 0.95 [34]
Mini-Mental Status Examination (MMSE) [36]	Convergent validity: *r* = 0.7 to 0.9 with other cognitive screening tests [37]	Test-retest reliability coefficients = 0.80 to 0.95 [37]	Inter-rater reliability was found to be high (mean kappa value = 0.97) [38]
Subjective Scale to Investigate Cognition in Schizophrenia (SSTICS) [13]	Convergent validity: the SSTICS total score positively correlated with the Frankfurt-Pamplona Subjective Experiences Scale total score (*r* = .541, *p* < .01) [39] Good internal consistency*:* Cronbach’s alpha = 0.858 [13]	Test-retest coefficient: *r* = 0.82 (*p* < 0.01) for the two global scores [13]	–
RL/RI-16 [40]	RL/RI-16 is sensitive enough to differentiate patients with Alzheimer’s disease from those with mild cognitive impairment [41], vascular dementia [14] and fronto-temporal dementia [42].	Use of a parallel form whose performances are not different from the basic list except for free recall 2 and delayed free recall (parallel form > basic list)	–
Doors test [15]	Moderately strong correlations with visual recognition memory task (*r*^2^ ≅ 0.60) [43].	–	Inter-rater reliability: excellent agreement (*r* = .98) between two independent raters in a sample of 237 subjects [44]
Test of attention D2 [16]	Internal consistency: Cronbach’s alpha = 0.97 for total score [45].	The ICCs for the seven subscores of the D2 between successive sessions were between 0.78 and 0.94 [46]	
The Rey-Osterrieth complex figure [17]	–	Test-retest reliability coefficients = 0.60 to 0.76 [47].	The inter-rater reliability for direct copying scores was *r* = 0.96 (*p* < 0.0001) [48].

*ICC* intra-class correlation coefficient

### Plans to promote participant retention and complete follow-up {18b}

No specific strategy is planned to promote participant retention. However, resistant schizophrenic patients are mostly long-term hospitalized patients because of their serious illness. Being hospitalized can guarantee adherence to care. As far as possible, if the patient wishes to stop ECT sessions, it is recommended to proceed to the next follow-up visit in order to have the most concomitant data of the end of the ECT.

### Data management {19}

All required information in the protocol should be recorded on the case report forms with an explanation for any missing data. The data should be collected as soon as the information is obtained. The data should be clearly transcribed in these forms. The mistaken data will be corrected by the investigator or the person allowed to make the relevant correction.

As the data are collected on an electronic case report form (eCRF), the traceability of amendments and updates is automatic (audit-trail).

### Confidentiality {27}

All the data collected in the eCRF are anonymized, that is to say that the patient receives a code name according to their inclusion center and their randomization number. Only their initials and their month and year of birth are noted. All documentation pertaining to the study (protocol, consent, case report forms, investigator folder, etc.) as well as original documents (laboratory results, neuroimaging data, consultation reports, reports of clinical examinations, etc.) will be kept in a safe place and considered as confidential material. Data archiving will be the responsibility of the investigator and in accordance with the laws in place. The investigator will retain the data as well as the patient identification list for a minimum period of 15 years after the end of the study.

### Plans for collection, laboratory evaluation, and storage of biological specimens for genetic or molecular analysis in this trial/future use {33}

None of these procedures is planned in the study.

## Statistical methods

### Statistical methods for primary and secondary outcomes {20a}

Patient characteristics will be described overall and by randomly allocated treatment arm (short or long therapy) using the usual parameters, i.e., mean, standard deviation, median, interquartile range, and range for quantitative characteristics and frequencies for categorical characteristics.

The main outcome (the response rate in the PANSS three months after treatment cessation) being categorical, Pearson’s chi-square test will be used. The same strategy will be applied for the other categorical criteria (secondary outcomes). For the secondary outcomes with quantitative measures, the comparison between both groups will be performed thanks to the repeated measures ANOVA or Mann-Whitney tests based on delta scores (i.e., month 6 minus baseline, month 15 minus baseline), when the assumptions of variance equality and/or normal distribution are violated. If multiple Mann-Whitney tests are performed, Bonferroni adjustment will be applied to compensate for the risk of type 1 errors.

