### Methods in analysis to handle protocol non-adherence and any statistical methods to handle missing data {20c}

Comparison of the two treatment arms will be based on the intent-to-treat principle. The maximum bias hypothesis shall be considered for non-assessed patients 3 months after the end of the treatment (patients lost to follow-up). Those patients, if in the group with the most favorable evolution, shall be considered as having not responded. On the contrary, those patients, if in the group with the most unfavorable evolution, shall be considered as responding to treatment. The aim is to reduce the gap between both to a minimum. By doing so, a robust conclusion is expected. Then, several sensitivity analyses shall be carried out: one analysis excluding patients lost to follow-up (per-protocol analysis) and another imputing the missing data by the last observed value (“last observation carried forward”).

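### For five clinical secondary scales, a data-triggered switch to Mann-Whitney tests leaves out four of six follow-up visits, and Bonferroni is tied to that branch alone

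*Protocol article*

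**What the plan says.** In the protocol article, Statistical methods for primary and secondary outcomes {20a}, the rule for all quantitative secondary measures is that "the comparison between both groups will be performed thanks to the repeated measures ANOVA or Mann-Whitney tests based on delta scores". A bracket defines the delta scores ("i.e., month 6 minus baseline, month 15 minus baseline"), and the trigger for the rank tests is "when the assumptions of variance equality and/or normal distribution are violated". On multiplicity there is one sentence: "If multiple Mann-Whitney tests are performed, Bonferroni adjustment will be applied to compensate for the risk of type 1 errors".

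The Secondary outcomes section gives two schedules. The five clinical scales (HAMD-21, YMRS, MOAS, CGI and GAF) are rated at every visit; the list ends with "Global Assessment Functioning (GAF) score at baseline and at 2, 4, 6, 9, 12, and 15 months" and continues "Changes from baseline will be compared between both groups". For the six cognitive measures (MMSE, SSTICS, RL/RI-16, Doors, D2 and Rey copy) it says "Changes between baseline and 6 months and between baseline and 15 months will be compared between the groups".

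Objectives {7} sets as a second aim the comparison of clinical symptoms over the whole course of the study. The missing-data section {20c} states intent-to-treat. Its main rule is a maximum-bias assignment of response status, and its sensitivity analyses are an analysis without patients lost to follow-up and last observation carried forward.

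**The concern.** The fallback does not fit the outcomes it has to serve. Five scales are measured at six post-baseline visits, yet if an assumption check fails the plan names changes at only two of them. One omitted visit is month 9, the short arm's assessment three months after treatment, which is half of the trial's primary comparison.

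The assumption check also decides two things at once: which test is used, and whether a multiplicity correction is applied. The same scale, with the same treatment effect, can thus be held to different standards according to the shape of its observed distribution.

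At stake is the second aim. Its answer could come from fewer visits, and with a significance level that is not fixed before the data are seen.

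**Working it through.** **1. The plan's own figure.** The Sample size section assumes response rates of 0.6179 and 0.2325, alpha 0.05 and power 0.80. For a two-sided test with pooled variance, the mean rate is 0.4252 and n = [1.96·√(2·0.4252·0.5748) + 0.8416·√(0.6179·0.3821 + 0.2325·0.7675)]² / 0.3854² = 24.6, so 25 per arm (power 0.806). With 20% drop-out, 25/0.80 = 31.25, so 32 per arm. The stated figures reproduce. They concern the primary outcome; no figure is given for the secondary scores.

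**2. Visits.** Setting the two schedules beside the fallback:

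| Scores | Scheduled post-baseline months | Months in fallback | Left out |
|---|---|---|---|
| HAMD-21, YMRS, MOAS, CGI, GAF | 2, 4, 6, 9, 12, 15 | 6, 15 | 2, 4, 9, 12 (4 of 6) |
| Six cognitive measures | 6, 15 | 6, 15 | none |

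The count of five follows the Secondary outcomes section. The abstract places SSTICS on the full visit schedule as well; on that reading six scales are affected.

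The two retained months do not put the arms at the same distance from the end of treatment. At month 6 the short arm has just finished and the long arm is halfway. At month 15 the long arm is 3 months past treatment and the short arm is 15 − 6 = 9 months past it.

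**3. How often the switch might occur.** The article names no check, so this is illustrative. Assume 25 patients per arm, two correlated changes per scale, Shapiro tests in each arm (four) and Levene tests (two), all at 5%. With truly normal data, 4,000 simulated trials switched 26% of the time. Six independent checks would give 1 − 0.95⁶ = 26.5%, which agrees. With lognormal data nearly every trial switched.

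**4. Multiplicity.** There are 5 + 6 = 11 scores. With one uncorrected test each at 0.05, if independent:
- five clinical scales: 1 − 0.95⁵ = 22.6%
- all eleven: 1 − 0.95¹¹ = 43.1%

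Positively correlated scales would give less. On the rank-test branch the per-test level depends on the family, which is not defined:
- two time points of one scale: 0.05/2 = 0.025
- eleven tests: 0.05/11 = 0.0045
- eleven scales at two time points: 0.05/22 = 0.0023

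**5. Patients (inference).** A classical repeated-measures ANOVA needs every visit. At the planned 20% drop-out it keeps at most 0.8 × 32 = 25.6 per arm, or 51.2 of 64. If drop-out falls evenly over the six visits (assumption), the observed post-baseline ratings number 64 × (6 − 0.2 × 21/6) = 339.2. Complete rows supply 51.2 × 6 = 307.2. The difference is 32 ratings, or 9.4%, and all 12.8 drop-outs contribute nothing.

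**The case against.** The strongest reply is that the switching rule is written in advance, that only secondary outcomes are involved, and that a fuller analysis plan may name the check, the Bonferroni family and the handling of missing scores. That is fair: silence on those details is not counted here. The point rests on what the article does state, namely the two-month fallback and the correction attached to one branch.

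The months in the bracket match the cognitive schedule exactly, so they may have been written with those tests in mind. That is possible, but the sentence governs all quantitative secondary outcomes, and the bracket is worded as a definition, not as an example.

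The Bonferroni sentence also has a rationale. An ANOVA treats a scale's visits in one model, whereas the fallback splits them into several tests. This justifies a correction within a scale. It leaves the eleven scales uncorrected on the ANOVA branch and unclear on the other.

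A reader might go further in four ways that the documents do not support:
- *The plan is complete-case and so breaks intent-to-treat.* No section says how incomplete scores enter the ANOVA. The loss of patients is a reasonable inference from the classical method, no more. Lower retention figures would need missed-visit rates that the documents do not give.
- *Familywise error is over 40% on one branch and 5% on the other.* If Bonferroni is applied within each scale, the error across eleven independent scales is also about 43% on the rank branch, and the contrast disappears.
- *Change scores waste baseline information by a known amount.* The usual gain from covariance adjustment is measured against a parametric change score. It does not measure the loss in a rank test, which is the only place where this section uses deltas.
- *PANSS and BPRS should not be reported as response rates.* That is a choice of endpoint, not an error.

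**Conclusion.** The point holds for the five clinical scales. If the assumption check fails, the stated fallback drops 4 of 6 post-baseline visits, including month 9. This does not fit the Secondary outcomes section or the second aim. No visits are lost on the ANOVA branch, or for the cognitive tests on either branch.

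For all eleven scores, the multiplicity correction depends on an assumption check on variance or normality. Its effect on error cannot be stated exactly, because the Bonferroni family is undefined; the 43% is an upper illustration under independence.

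The loss of patients, to about 25.6 of 32 per arm, is conditional on a classical ANOVA and the planned drop-out. No main missing-data rule in the article covers these scores: maximum bias fits only responder status, and last observation carried forward is a sensitivity analysis.

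The primary chi-square test and the sample size are untouched. This is a worthwhile and cheap improvement to the secondary analysis, not a threat to the main result.

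**What to change.** Prespecify one likelihood-based mixed model for repeated measures per quantitative scale, with arm, visit, arm-by-visit, baseline value and centre, using every observed visit. If residuals are skewed, use robust or bootstrap intervals instead of changing the test, and keep the Mann-Whitney comparison as a sensitivity analysis.

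State two kinds of contrast separately: same-month differences between arms, and the comparison three months after treatment (month 9 short against month 15 long). They answer different questions, since at month 9 the long arm is still under treatment.

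Apply one multiplicity rule with a defined family to the secondary scores, or label them exploratory, whichever test is used.

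The cost is some wording, slightly more analysis work and an explicit missing-at-random assumption. That assumption should be stated openly, because the discontinuation criteria include clinical worsening and a short-arm patient's wish for more ECT. No new data are needed.

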## Discussion

Even though ECT is recommended for patients with URS, there is a noticeable lack of rigorous studies on this subject. Parameters such as the frequency of ECT sessions, the position of electrode(s), the seizure efficacy criteria, or the anesthetic management have been little studied and should be tested. In addition, the utility of maintenance ECT in patients with URS has never been studied, except in open studies and clinical cases. The present study focuses on the optimal duration of ECT treatment, aiming to compare two protocols of combining ECT with clozapine: a 6-month protocol and a 12-month protocol.

The minimum number of ECT sessions to achieve significant clinical improvement in patients with URS ranges between 16 and 20 [49, 50]. In a recent meta-analysis about ECT augmentation of clozapine for clozapine-resistant schizophrenia, the mean duration of the included studies was only 8–9 weeks [4]. The authors suggested that longer-term follow-up data are needed in order to assess if patients maintain the clinical improvement that they achieved from ECT augmentation of clozapine, or whether maintenance ECT is required. The present study should try to answer this important question. We hypothesized that the long protocol will be more effective than the short protocol. It is important to accurately assess the efficiency gain because an increased duration of treatment leads to an additional cost and decreases the number of potentially treated patients. A long protocol could also allow a better stabilization of patients, avoid relapses and hospitalizations, and thus improve their cognitive profile and their quality of life.

Some methodological choices we made are worth discussing.

First, the duration of participation in this study is long (15 months in total). There is therefore a risk of having a significant number of patients lost to follow-up, especially in severely disabled patients. In the sample size calculation, the drop-out rate was estimated to 20% and the number of patients increased to overcome the reduction of statistical power. However, we lack data to accurately estimate this rate.

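### Quantitative secondary scores: repeated measures ANOVA needs every visit and no main missing-data rule covers scores, so the analysis would default to completers

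*Protocol article*

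**What the plan says.** - **Method.** Statistical methods {20a} states for quantitative secondary outcomes that "the comparison between both groups will be performed thanks to the repeated measures ANOVA". If equal variances or normality fail, the protocol moves to Mann-Whitney tests on the change from baseline to months 6 and 15, with a Bonferroni adjustment when several are done.
- **Visits.** Under Secondary outcomes {12}, HAMD-21, YMRS, MOAS, CGI and GAF are measured "at baseline and at 2, 4, 6, 9, 12, and 15 months. Changes from baseline will be compared between both groups", which is seven visits. The cognitive tests have three: baseline, 6 and 15 months.
- **Analysis principle.** Section {20c}: "Comparison of the two treatment arms will be based on the intent-to-treat principle".
- **Missing data.** The main rule in {20c} is a maximum-bias rule. Patients not assessed three months after treatment count as non-responders in the better arm and as responders in the worse arm. Two sensitivity analyses follow: one excludes patients lost to follow-up (called per-protocol), the other carries the last observation forward.
- **Expected loss.** Sample size {14}: "To overcome an estimated 20% drop-out, the required number of patients increased to 32 patients per group". The Discussion adds "There is therefore a risk of having a significant number of patients lost to follow-up" and, on the drop-out figure, "However, we lack data to accurately estimate this rate".
- **Exits.** The exit criteria in {10} and the discontinuation criteria in {11b} let the investigator end participation for clinical worsening, adverse effects or a needed change of background drugs. Section {11b} adds a reason that can arise only in the short arm: the patient's wish for more ECT.

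**The concern.** The named method and the stated analysis principle do not fit together for scores. Classical repeated measures ANOVA needs a full row of visits from each patient, so one missed visit removes all of that patient's data. The maximum-bias rule cannot fill the gap, because it assigns responder or non-responder status and a HAMD-21 or GAF score has no such status. What remains by default is a completer analysis. For the responder endpoint the protocol itself treats excluding patients lost to follow-up as a sensitivity analysis. For scores, that exclusion would become the main analysis.

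At stake are the score-based comparisons of clinical course over the study and the cognitive comparisons, including the attention hypothesis in Objectives {7}. If exits follow worsening, or arise in one arm for a reason that cannot arise in the other, those who complete all visits may differ from those randomised, and differ by arm.

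A secondary worry is the arm-by-time F test, which assumes sphericity. Assessments two months apart usually correlate more strongly than assessments fifteen months apart, and {20a} names only equal variances and normality as the assumptions that trigger its fallback.

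**Working it through.** **The plan's own figure first.** Section {14} assumes that "the responder rates would be 61.79% in the long ECT protocol and 23.25% in the short ECT protocol", and continues: "Assuming an alpha risk of 0.05 and a power of 0.80, we estimated the need to include 25 patients per group". With two-sided alpha, pooled variance and no continuity correction, the mean rate is (0.6179 + 0.2325)/2 = 0.4252 and the difference is 0.3854:

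n = [1.960·√(2·0.4252·0.5748) + 0.8416·√(0.6179·0.3821 + 0.2325·0.7675)]² / 0.3854² = (1.370 + 0.542)² / 0.1485 ≈ 24.6, so 25 per arm.

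Then 25/0.8 = 31.25, so 32 per arm and 64 in total. The figure reproduces (power at 25 per arm is 80.6%). The protocol gives no corresponding figure for the ANOVA.

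**Complete cases.** Inputs: 64 patients and 20% drop-out, both from {14}; six or two post-baseline visits, from {12}; probability p of missing any one visit independently, which is my assumption.

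Expected complete cases = 64 × 0.8 × (1 − p)^m, with m = 6 or 2.

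| p | Seven visits (m = 6) | Three visits (m = 2) |
|---|---|---|
| 0 | 51.2 | 51.2 |
| 2% | 51.2 × 0.886 = 45.4 | 51.2 × 0.960 = 49.2 |
| 5% | 51.2 × 0.735 = 37.6 | 51.2 × 0.9025 = 46.2 |

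On the seven-visit scales, about 13 (64 − 51) to 26 (64 − 38) randomised patients would contribute nothing, although many would have recorded visits.

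**Which missing-data rule reaches a score?**
- Maximum bias: main rule, responder status only.
- Excluding patients lost to follow-up: sensitivity analysis, and itself a completer analysis.
- Last observation carried forward: applicable to scores, but named only as a sensitivity analysis.

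No main rule for scores is left.

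**Sphericity, as a supporting point.** I simulated the two-arm ANOVA with no true difference, 10,000 trials per setting, 25 and 32 per arm. The uncorrected arm-by-time F has k − 1 and (k − 1)(2n − 2) degrees of freedom, for example 6 and 288 at k = 7 and n = 25. The Greenhouse-Geisser version multiplies both by the estimated epsilon. The correlation patterns are assumptions, because the protocol gives none.

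| Rejection rate at nominal 5% | Seven visits | Three visits |
|---|---|---|
| Compound symmetry, uncorrected | 5.0% | 5.0% |
| Correlation decaying with time, uncorrected | 6.8-9.7% | 5.2-5.9% |
| Random intercept and slope, uncorrected | 7.0-7.6% | 5.6-6.0% |
| All patterns, Greenhouse-Geisser | 4.2-5.2% | 4.6-5.1% |

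A further 20,000 runs with 26 per arm, seven visits and correlation 0.6-0.9 between visits three months apart gave 8.0-10.0% uncorrected. Adding 20% independent measurement noise brought this to 6.4-6.7%. The test of the arm main effect stayed at 4.7-5.5% throughout.

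**The case against.** A reader might infer that the secondary results are not intent-to-treat and that the arm-by-time test will be significant too often. The protocol supports neither as a statement of fact.

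- **Dropping patients is not stated.** Section {20a} does not say that incomplete patients are removed, {20c} commits to intent-to-treat, and carrying the last observation forward would give the ANOVA complete rows. This stands in part: the conflict follows from the method's default and is not a declared rule. It does not settle the matter, because that imputation is reserved for sensitivity analysis.
- **An uncorrected test is not stated.** An epsilon correction is ordinary analysis-plan detail, and that plan is not shown. The inflation also needs an arm-by-time test on all seven visits with decaying correlation. This stands, so sphericity cannot carry the point alone.
- **Reach.** It is tempting to say that the whole second aim rests on completers. It does not: PANSS and BPRS enter as response rates, which go to a chi-square test. Attention (D2) has three visits, where the loss is smaller and the inflation slight.
- **The fallback.** Mann-Whitney on change scores needs only baseline and the visit compared, and it has no sphericity assumption. Because current mood episodes are excluded, YMRS and HAMD-21 may be skewed enough to trigger it. This narrows the problem, but the fallback depends on distribution and not on missingness, and it still leaves out patients without the visit in question.
- **Retention may be good.** Section {18b} expects mostly long-stay inpatients and recommends going to the next follow-up visit when ECT is stopped. The missed-visit rates above are therefore assumptions. The 20% drop-out is the protocol's own.

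**Conclusion.** The point holds for the quantitative secondary scores. The first-line method needs complete rows, the main missing-data rule does not reach scores, and the analysis would default to completers against the stated principle. At the protocol's own drop-out, at most about 51 of 64 patients would be used. With a further 2-5% of visits missed (assumed), that falls to about 45-38 at seven visits or 49-46 at three. Completers may be a selected group, given how exits are defined, but the protocol offers no basis for stating the direction or size of any bias.

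The sphericity point is supporting only. An uncorrected arm-by-time test on seven visits would reject in roughly 6.5-10% of null trials if correlation decays with time. There is no inflation under compound symmetry or for the arm main effect, and little at three visits.

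The primary chi-square test, the sample size and the PANSS and BPRS response rates are untouched. The change should be made before analysis, but it does not threaten the trial's main conclusion.

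**What to change.** In {20a}, replace repeated measures ANOVA by a likelihood-based mixed model for repeated measures:
- visit as a category, with an arm-by-visit term;
- unstructured covariance, with a simpler structure named in advance in case of non-convergence;
- all recorded visits of randomised patients, apart from data that the exit criteria remove on withdrawal of consent;
- arm contrasts at the planned visits.

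Section {20c} should then name this model as the main handling of missing scores. Any ANOVA kept as a supportive analysis should use a Greenhouse-Geisser correction.

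The cost is a sentence or two and standard software, with no new data or patients. There are two downsides. The unstructured covariance may not converge with 64 patients, hence the named fallback. The model also relies on data being missing at random, so it does not remove bias from exits that depend on scores never recorded.
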